Because the incidence rates of certain complications of interest are small, we require a large sample size to observe sufficient numbers of each complication. During initial study planning, we calculated a sample size of 15,000 participants across three countries (four sites), with enrollment evenly distributed among the countries. However, with start-up and accrual delays owing to the SARS-CoV2 pandemic, we conducted a modified analysis to assess the impact of a reduced sample size of 12,000 on our key analytic goals. To do this, we performed a 2-part simulation study to assess our expected ability to (1) estimate risk and (2) estimate optimal decision rules. For (1), we assessed the anticipated precision with which we would be able to estimate risk for key outcomes using exact Poisson confidence intervals
^
16
^. Basing our estimates on observed event rates in the first 500 participants in the study, we expect to estimate a rare event, one occurring in just 2% of the participants, with 95% confidence intervals with a half-width of 1.2%. For (2), using the first 500 observations in the study and 9 key covariates, we generated simulation data sets by sampling with replacement from the observed covariates and constructing binary treatment decisions for each simulation record conditional on covariates. We also generated outcomes for each simulation record such that individual treatment effects exhibited heterogeneity dependent on interactions between the treatment and patient covariates. For each simulation data set, we estimated an optimal treatment rule that tailors treatment recommendations based on patient features. Across replications, we estimated the probability of correctly rejecting the null hypothesis that there is no benefit of personalized decision-making when compared to completely randomized decision-making (i.e., a coin flip). With a true risk ratio of 1.17 and a sample size of 12,000 participants, our analysis indicates a 76% probability of correctly rejecting the null hypothesis. Our simulation results further indicate that an overall sample size of 12,000 yields sufficient power for estimating decision rules that, when used to recommend treatments, will reduce the probability of observing a bad outcome sufficiently close to the true optimal.

**
*Statistical analysis*
**

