## Discussion

Provision of quality obstetrical and neonatal health care is a complex matter that requires informed patients, trained providers, equipped and proximal facilities, timely diagnostics, an uninterrupted supply of essential treatments, and a coordinated strategy for all individual components to operate harmoniously
^
33
^. Obstetrical and neonatal services in resource-limited settings often lack some or all of these critical components. Algorithms that identify the maternal-fetal dyads at greatest risk for preventable intrapartum complications would allow the targeting of limited resources toward those that need it most and are the most likely to benefit.

The overarching goal of our research is to develop new tools that can be deployed in low-resource healthcare facilities to improve intrapartum outcomes through better risk stratification, timely intervention or transfer to higher care, and earlier diagnosis. The first step toward this goal is to precisely characterize the incidence of adverse labor outcomes and their measurable antecedents in diverse populations while carefully documenting patterns of care. The data generated by this study will serve as a foundation for new discovery and development of novel technological approaches to substantially reduce adverse perinatal outcomes. With this study, we aim to create the largest, most extensively documented observational cohort of labor and delivery ever assembled.

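### The stated 95% CI half-width of 1.2% for a 2% event does not follow from 12,000 participants; the named exact Poisson method gives about 0.26 percentage points

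*Protocol article*

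**What the plan says.** The Sample size section explains that the planned cohort was cut from 15,000 to 12,000 after pandemic delays, and that "we conducted a modified analysis to assess the impact of a reduced sample size of 12,000 on our key analytic goals". It then describes how: "To do this, we performed a 2-part simulation study to assess our expected ability to (1) estimate risk and (2) estimate optimal decision rules". For the first part, "we assessed the anticipated precision with which we would be able to estimate risk for key outcomes using exact Poisson confidence intervals". The event rates come from the start of the study: "Basing our estimates on observed event rates in the first 500 participants in the study". The only numerical result of this part is that "we expect to estimate a rare event, one occurring in just 2% of the participants, with 95% confidence intervals with a half-width of 1.2" percent.

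On allocation, the same section says of the original plan that "we calculated a sample size of 15,000 participants across three countries (four sites), with enrollment evenly distributed among the countries". The Study setting section lists one site in Ghana, one in Zambia and two in India. No subgroup, design effect, clustering adjustment or missing-data allowance is attached to the precision figure.

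**The concern.** The rate, the confidence level, the interval method and the cohort size all stand in one paragraph, so the half-width can be checked directly. A half-width of 1.2 points around 2% means knowing the risk only to roughly 0.8% to 3.2%, which is poor for a cohort of this size and looked too wide on sight.

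It matters because this is the only precision figure offered for the reduced sample; the other support is the decision-rule power in the second part. The Discussion says that "The first step toward this goal is to precisely characterize the incidence of adverse labor outcomes and their measurable antecedents in diverse populations". That sentence sets no numerical target, so no stated criterion is breached, but a reader who takes 1.2% at face value would conclude that 12,000 women estimate rare outcomes badly. The figure also cannot show what the loss of 3,000 participants costs.

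**Working it through.** **Inputs, all from the Sample size section unless noted**
- Cohort: n = 12,000 (originally 15,000)
- Event risk: 2%, so expected events x = 0.02n
- Two-sided 95% interval, exact Poisson
- Stated half-width: 1.2%, read as percentage points
- Allocation: even by country. This is stated for the 15,000 plan and assumed here to carry over to 12,000, giving 4,000 per country. The two Indian sites (Study setting) are assumed to share India's 4,000 equally, 2,000 each.

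**Formula**

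Lower = χ²(0.025; 2x) / (2n); upper = χ²(0.975; 2x + 2) / (2n); half-width = (upper − lower) / 2.

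**Step 1: try to reproduce the stated figure at 12,000**

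x = 0.02 × 12,000 = 240. The interval is 1.755% to 2.270%, so the half-width is (2.270 − 1.755) / 2 ≈ 0.257 points. The stated figure is not reproduced: 1.2 / 0.257 ≈ 4.7.

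**Step 2: try other readings at 12,000**

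| Reading | Result |
|---|---|
| Wald (binomial) half-width | 0.250 points |
| Clopper-Pearson half-width | 0.255 points |
| Full width of the exact Poisson interval | 0.51 points |
| Upper arm only | 0.27 points |
| 99.99% confidence, half-width | 0.51 points |
| Half-width relative to the 2% risk | 0.257 / 2 ≈ 12.9% |

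None gives 1.2. At this n, an exact Poisson half-width of 1.2 points would need an event risk of about 45%.

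**Step 3: try other sample sizes (exact Poisson, 2% risk)**

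| n | Events | Half-width (points) |
|---|---|---|
| 15,000 (original cohort) | 300 | 0.23 |
| 12,000 (reduced cohort) | 240 | 0.26 |
| 4,000 (a country, or the single site in Ghana or Zambia) | 80 | 0.45 |
| 2,000 (each Indian site) | 40 | 0.65 |
| 500 (first participants) | 10 | 1.36 |

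The half-width rounds to 1.2 only for n of about 583 to 678.

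**Step 4: design effect needed to reach 1.2 at 12,000**

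(1.2 / 0.257)² ≈ 22. With three equal countries of 4,000, that corresponds to an intraclass correlation of about (22 − 1) / 3,999 ≈ 0.005.

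**The case against.** **The sentence carries no sample size of its own.** In that paragraph 12,000 is attached explicitly to the second-part results, and the article condenses a fuller simulation report, so 1.2% might belong to a stratum whose size was dropped. This stands as a reason to let the authors name that stratum. It does not rescue the sentence: the calculation is introduced as the assessment of 12,000, and the event is described as occurring in 2% of the participants, with no subset mentioned.

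**Clustering could widen the interval.** A design effect of 22 sounds extreme, but with a few very large clusters it needs an intraclass correlation of only about 0.005. So 0.26 should be labelled as assuming independent observations. Even so, the section mentions no such adjustment, and a plain exact Poisson interval contains none.

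**The error is harmless in direction.** True precision is better than stated, no endpoint or analysis changes, and the Study status section reports that follow-up finished in September 2022. This stands, and it limits the severity to a correction of reporting.

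**A reader might infer that the first 500 participants were used in place of 12,000.** A Wald interval at 500 does give 1.23. But the article names exact Poisson intervals, which give 1.36 at 500, rounding to 1.4. The article presents the 500 only as the source of event rates. The explanation is possible, not shown.

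**Conclusion.** The figure is wrong as written and should be corrected. Under the article's own rate, method and cohort size, the half-width is about 0.26 percentage points, and the printed 1.2% is about 4.7 times that. No planned unit of the design gives 1.2: the cohort, country and site sizes run from 0.26 to 0.65. How the figure arose is unknown.

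The result for the whole cohort assumes independent observations, complete outcome data on 12,000 women and an observed risk of exactly 2%. The country and site values also assume the allocation set out above.

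A reader might go further and infer that 12,000 is too few to characterise incidence. The documents do not support that. The correct figure strengthens the precision argument: going from 15,000 to 12,000 moves the half-width from 0.23 to 0.26 points, a cost of about 0.03. The 76% power result for decision rules is a separate argument and is not affected.

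**What to change.** Replace 1.2% with 0.26 percentage points, and say that this is the exact Poisson half-width for a 2% event at n = 12,000 with observations treated as independent. Optionally add 0.23 at the original 15,000, so that the cost of the reduction can be read off.

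If 1.2% was intended for a subgroup or includes a design effect, keep it but state the subgroup size or the design effect beside it.

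Do not add a per-site figure obtained by dividing 12,000 by four (3,000 women, 0.52 points). It conflicts with an even split by country when India has two sites.

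The cost is one corrected sentence, with no change to design, conduct or analysis.

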### Data analysis and statistical plan

**
*Study outcomes*
**

The primary outcomes of the LABOR Study include a composite maternal outcome of potentially actionable incident adverse events and a composite fetal / neonatal outcome of the same nature (
Table 2). Secondary outcomes include the individual components of the two primary composite outcomes: maternal outcomes including maternal death, incident intrapartum hemorrhage, postpartum hemorrhage, incident hypertensive disorders (eclampsia, severe preeclampsia, preeclampsia, superimposed preeclampsia, severe gestational hypertension), and incident maternal infection (intrauterine inflammation or infection, endometritis), and fetal / neonatal outcomes including intrapartum stillbirth, neonatal death, encephalopathy, and sepsis. The LABOR Study distinguishes between prevalent conditions (those present at the time of enrollment) and incident conditions (those arising after enrollment). Although we identify and assess frequency of prevalent conditions, the primary focus of analytic approaches described below is the characterization and prediction of incident conditions.

**Table 2. T2:** Study outcome definitions.

Maternal Outcomes	
Maternal death	Death of a maternal participant after study enrollment and up to 42 days postpartum, irrespective of cause
Incident intrapartum hemorrhage	Intrapartum vaginal bleeding of ≥ 1000 mL of blood prior to delivery of the placenta
Postpartum hemorrhage	Blood loss of ≥ 1000 mL or any bleeding leading to an adverse event, regardless of mode of delivery, either within the 24 hours after delivery of the placenta (primary) or up to 42 days postpartum (secondary)
Incident eclampsia	New onset of tonic-clonic, focal, or multi-focal seizures in the absence of other causative conditions
Incident severe preeclampsia	New development of systolic blood pressure ≥ 140 mmHg or diastolic pressure ≥ 90 mmHg measured at least 4 hours apart in addition to proteinuria and at least one of the following severe features: thrombocytopenia, renal insufficiency, impaired liver function, pulmonary edema, new-onset cerebral or visual disturbances, or rise in systolic blood pressure to ≥ 160 mmHg or diastolic pressure to ≥ 110 mmHg
Incident preeclampsia	New development of systolic blood pressure ≥140 mmHg or diastolic pressure ≥ 90 mmHg measured at least 4 hours apart in addition to proteinuria in the absence of severe features described above

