*Descriptive analysis of baseline, intrapartum, and outcome variables.* Common methods for descriptive statistics will be used to examine the distribution of key baseline factors, intrapartum events, and overall outcomes in the study population (e.g., frequencies for categorical variables and measures of centrality and dispersion for quantitative variables). These methods will also be used to examine unadjusted (crude) differences in the distribution of outcomes and intrapartum events by baseline factors. Key baseline factors will include maternal demographics, medical history and obstetrical risk factors, enrollment ultrasound, physical examination and laboratory values collected at admission or enrollment in the study. Intrapartum events will include time-varying variables related to the course of labor (e.g., cervical examinations), provider interventions (e.g., drugs, procedures), and continuous monitoring through fetal and maternal sensors.

*Associations between baseline variables, interventions, and outcomes.* Generalized linear models will be used to estimate the adjusted relative risk with 95% confidence interval of outcomes associated with baseline factors. Covariates (baseline factors) for inclusion in the multivariable models will be identified
*a priori* based on clinical relevance and using causal directed acyclic graphs. We will start by fitting two separate models for binary outcome variables (yes/no) for the composite maternal and fetal / neonatal outcomes, respectively. If baseline factors of interest are found to be associated with the composite outcomes, we will fit models to each of the individual outcome components within each composite (maternal or fetal / neonatal). A similar modeling approach to that used for the composite and individual outcomes will be used to estimate associations between baseline factors (covariates) and key intrapartum interventions such as cesarean delivery.

*Predictive models and risk stratification.* We will develop and validate models to use baseline variables to predict the probability of each outcome. These predicted probabilities can be used to stratify patients by risk. Because of the expected high dimensionality of the data, we will consider the use of dimension reduction techniques such as deep learning autoencoders
^
17

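### Adjusted models for the component outcomes depend on an association with the composite, so effects specific to one component, or in opposite directions, can be missed.

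*Protocol article*

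**What the plan says.** Under Study outcomes, the article gives the components formal standing: "Secondary outcomes include the individual components of the two primary composite outcomes". Table 2 then defines ten maternal and four fetal or neonatal components.

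Under Statistical analysis, in the paragraph on associations between baseline variables, interventions and outcomes, the target is an adjusted relative risk: "Generalized linear models will be used to estimate the adjusted relative risk with 95% confidence interval of outcomes associated with baseline factors". The order of fitting follows: "We will start by fitting two separate models for binary outcome variables (yes/no) for the composite maternal and fetal / neonatal outcomes, respectively". The next sentence sets the condition: "If baseline factors of interest are found to be associated with the composite outcomes, we will fit models to each of the individual" components. No threshold for an association is given, and no other route to an adjusted component relative risk is described.

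Two nearby analyses carry no such condition. The descriptive paragraph says "These methods will also be used to examine unadjusted (crude) differences in the distribution of outcomes and intrapartum events by baseline factors". The paragraph on predictive models says "We will develop and validate models to use baseline variables to predict the probability of each outcome".

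**The concern.** The maternal composite pools death, hemorrhage, hypertensive disorders and infection, which need not share risk factors. A factor that acts on one of them is diluted by events it does not affect. A factor that raises one and lowers another can leave the composite unchanged. If the composite result decides whether that factor's component models are fitted, the adjusted estimate for a named secondary outcome depends on the behaviour of other outcomes.

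This fits poorly with the study's own reasoning. The Sample size section justifies the large cohort by the need to see enough events of each complication, and the Discussion gives the characterization of outcomes and their antecedents as the first step. There is also a reporting effect: component estimates that appear only after the composite has passed a test are a selected set and tend to lie further from the null than the truth.

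**Working it through.** The article states no figure on this point, so there is none to reproduce. The check has two parts: what the condition covers, and how much it could cost.

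**Scope.** Three component-level analyses are planned: crude differences by baseline factor (unconditional), predictive models for each outcome (unconditional) and adjusted relative risks (conditional). Only the third is at risk. The other two do not replace it: crude differences are unadjusted, and the predictive models are built and assessed for prediction, not to give an adjusted relative risk with covariates chosen from causal diagrams.

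**Inputs from the article.** N = 12,000, from the Sample size section ("we conducted a modified analysis to assess the impact of a reduced sample size of 12,000 on our key analytic goals"), and a 2% event rate, its own example of a rare event.

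**Assumed inputs.** Exposure 20% or 50%; component RR 1.5; risk of the rest of the composite 5%, 10% or 13%, unaffected by the factor; component and rest mutually exclusive; two-sided 0.05 as the meaning of associated; gate applied to each factor; unadjusted two-group comparison.

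**Hand calculation, exposure 20% (2,400 exposed, 9,600 unexposed), rest 13%.** Power = Φ(|ln RR|/SE − 1.96), with SE = √[(1−p1)/(p1·n1) + (1−p0)/(p0·n0)].

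- Component: p0 = 0.02, p1 = 0.03. SE = √[0.97/72 + 0.98/192] = 0.136; ln 1.5 = 0.405; power = Φ(1.015) = 0.845.
- Composite: p0 = 0.02 + 0.13 = 0.15, p1 = 0.03 + 0.13 = 0.16, RR = 1.067. SE = √[0.84/384 + 0.85/1,440] = 0.0527; ln 1.067 = 0.0645; power = Φ(−0.735) = 0.231.

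**Simulation.** The two tests share events, so their joint result was simulated: 200,000 studies per row, binomial draws, pooled two-proportion z-tests at 1.96. The last column is the geometric mean component RR among studies where the gate opens.

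| Exposure | Rest | Composite RR | Component significant | Gate opens | Significant, gate closed | Mean gated RR |
|---|---|---|---|---|---|---|
| 20% | 5% | 1.143 | 82% | 40% | 44% | 1.61 |
| 20% | 10% | 1.083 | 82% | 27% | 57% | 1.61 |
| 20% | 13% | 1.067 | 82% | 23% | 60% | 1.60 |
| 50% | 5% | 1.143 | 94% | 55% | 40% | 1.57 |
| 50% | 10% | 1.083 | 94% | 38% | 57% | 1.58 |
| 50% | 13% | 1.067 | 94% | 33% | 62% | 1.57 |

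Without the gate the mean RR is 1.49 to 1.50 in every row.

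**Boundaries, exposure 50%.**

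- Opposite effects: component 2% with RR 2.0, rest 10% with RR 0.8. Exposed risk is 0.04 + 0.08 = 0.12, equal to the unexposed 0.02 + 0.10 = 0.12, so the composite RR is 1.00. The gate opens in 5% of studies and the component effect is passed over in 95%.
- Large effect: component 2% with RR 2.0, rest 5%. The gate opens in 98% of studies, so almost nothing is lost.

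**The case against.** A reader might infer that component effects are never estimated. The article does not support that, because the crude comparisons and the predictive models are planned without the condition. A reader might also infer that masking is certain. It is not, as the large-effect case shows.

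The strongest objection concerns the unit of the condition. The sentence is plural, and the surrounding text describes multivariable models with covariates chosen in advance. It can be read to mean that once some factors are associated with a composite, full multivariable models are fitted to every component, giving estimates for all factors. The gate would then open far more often. Even at 0.231 power per factor, with independence, 1 − 0.769^10 = 0.93 for ten factors and 1 − 0.769^20 = 0.99 for twenty (both counts are assumed). On that reading the losses in the table do not apply and most of the upward selection disappears. The wording is also *if*, not *only if*. This objection stands as a limit on size. It does not settle the text, which fixes neither the unit nor the criterion.

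Other points have some weight. Composite-first ordering can be defended as restraint on multiplicity, though the article gives no such reason. Very rare components, such as maternal death, may not support an adjusted model. The dilution argument is made here for the maternal composite; fetal and neonatal components may overlap more, and the calculation assumes no overlap.

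**Conclusion.** The concern holds in a limited form and is worth acting on. As written, the adjusted relative risk and 95% confidence interval for a named secondary outcome depend on the result for the composite. If the condition is applied factor by factor, a moderate effect on a single 2% component (RR 1.5) is detectable but gated out in about 40% to 62% of studies, and the estimates that do appear average about 1.57 to 1.61 against 1.50. With opposing effects the loss can be nearly complete; with a large effect or a dominant component it is small.

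These figures are illustrations. Only the 12,000 and the 2% come from the article. Exposure, the rest of the composite, the relative risks, the 0.05 criterion and the factor-by-factor gate are assumptions.

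**What to change.** Delete the condition. Fit the pre-specified adjusted model for each component whatever the composite result, wherever event counts allow, and report components too rare to model, such as maternal death, descriptively. Keep the composite models as primary, label the component models secondary, give 95% confidence intervals, and state how many models were fitted.

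Follow-up ended in September 2022, so this needs no new data: one changed sentence and additional model runs. The downside is more secondary estimates and comparisons to report and interpret, across up to fourteen components, some of them sparse.

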^, a nonlinear feature extraction tool using artificial neural networks, to reduce the dimension of baseline data prior to modeling, as well as, when appropriate, inclusion of regularization techniques such as elastic net
^
18
^. Predictive models will be fit using multiple machine learning techniques such as random forests
^
19
^, reinforcement learning trees
^
20
^, and kernel support vector machine
^
21
^. Model selection and validation will be done within a cross-validation framework with models fit using a training set, hyperparameters tuned using a validation set, and performance assessed on a testing set. For binary outcomes, model fit may be assessed using metrics such as accuracy, and for continuous outcomes, model fit may be assessed using metrics such as root mean squared error (RMSE). Key features identified in the predictive modeling will help us identify potential tailoring variables to be included in subsequent data-driven clinical decision support algorithms.

*Signal processing and dimension reduction.* The expected availability of multiple streams of physiological signals including maternal heart rate, contractions, and fetal heart rate in risk prediction models and clinical decision support algorithms is a unique opportunity. Yet, given the differences in the volume and velocity between these high-dimensional signal data and more standard clinical examination and laboratory data elements, some signal processing including possibly dimension reduction and feature extraction will be needed before the various types of data can be integrated into statistical learning models. A number of signal processing strategies are available; for example, Fourier decomposition methods may be used to analyze the nonlinear and non-stationary time series
^
22
^, the aforementioned autoencoder
^
23
^ may be used to reduce signal dimensionality to a parsimonious class of features, and modern deep learning may be used on the raw signal directly to extract and construct novel, highly predictive features.

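### Accuracy, the only example metric named for the binary prediction models, says almost nothing about outcomes near 2% and does not measure calibration or ranking at any rate

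*Protocol article*

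**What the plan says.** All of this is in the protocol article, Data analysis and statistical plan.

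- **Product.** Under Predictive models and risk stratification: "We will develop and validate models to use baseline variables to predict the probability of each outcome". The next sentence gives the use: "These predicted probabilities can be used to stratify patients by risk".
- **Framework.** "Model selection and validation will be done within a cross-validation framework with models fit using a training set", with hyperparameters tuned on a validation set and performance assessed on a test set. That sentence names no metric.
- **Metric.** The following sentence reads: "For binary outcomes, model fit may be assessed using metrics such as accuracy". Its second half gives root mean squared error as the matching example for continuous outcomes. No measure of discrimination or calibration, and no measure suited to rare events, is named.
- **Rarity.** The paragraph on sample size opens with this reason: "Because the incidence rates of certain complications of interest are small, we require a large sample size to observe sufficient numbers of each complication". The worked illustration is in these words: "we expect to estimate a rare event, one occurring in just 2% of the participants".
- **Outcomes covered.** Under Study outcomes, the individual components of both composites are secondary outcomes, so a model for each outcome includes the rarer components. No event rate is given for either composite or for any component.

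**The concern.** The intended output is a probability that places women on a risk scale. Accuracy does not score a probability. It scores a yes/no label after a cut-off has been applied, and it counts a missed event and a false alarm equally. Two models with quite different calibration, or quite different ordering of women by risk, can have the same accuracy.

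Rarity adds a second problem. When few women have the event, nearly all of the accuracy comes from the women without it, and a rule that never predicts the event scores close to 100%. If accuracy were used to compare candidate models for a rare component, the comparison would have little to work with, and a reported figure near 98% could be mistaken for good performance. The same paragraph carries the key predictive features forward as possible tailoring variables for decision-support algorithms, so a poor comparison at this step could affect later work.

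**Working it through.** **Inputs.** Rate p = 2% and n = 12,000 come from the Sample size section. The 2% is the article's illustrative rare event and not a stated rate for any outcome. AUCs of 0.70, 0.80 and 0.90, the equal-variance binormal form, the higher rates and the sensitivity/specificity pairs are assumptions, shown as ranges.

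**The plan's own figure.** The article states no accuracy or other model-performance figure to reproduce. The only figure tied to the 2% rate is a confidence-interval half-width of 1.2%. By exact Poisson limits that half-width is 0.26% at n = 12,000, 1.36% at n = 500 and 1.23% at n = 600. This is a separate matter, and nothing below depends on it.

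**Step 1: the no-model benchmark.** With sensitivity Se and specificity Sp,

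accuracy = p × Se + (1 − p) × Sp.

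Flagging nobody means Se = 0 and Sp = 1, so accuracy = 1 − p = 98.0% at p = 2%. A model beats this only if p × Se > (1 − p) × (1 − Sp), which is the same as PPV above 50%. With Se = 80% at p = 2%, that needs Sp above 1 − 0.02 × 0.80/0.98 = 98.4%.

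**Step 2: a model with Se = 80%, Sp = 90%.** Of 12,000 women, 240 have the event and 11,760 do not. The model finds 0.80 × 240 = 192 events with 0.10 × 11,760 = 1,176 false positives. Accuracy = (192 + 10,584)/12,000 = 89.8%, below the 98.0% of a rule that finds none. Other assumed pairs at 2%: 90/90 gives 90.0%, 70/95 gives 94.5% and 50/98 gives 97.0%.

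**Step 3: the best accuracy a model can reach.** Let scores be N(0,1) without the event and N(d,1) with it, where d = √2 × Φ⁻¹(AUC). For AUC 0.80, d = 1.4142 × 0.8416 = 1.190. The accuracy-maximising cut-off is where the model's probability equals 0.5:

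t = d/2 + ln[(1 − p)/p]/d = 0.595 + 3.892/1.190 = 3.865.

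Then Se = 1 − Φ(3.865 − 1.190) = 0.0037, Sp = Φ(3.865) = 0.999944, and accuracy = 0.02 × 0.0037 + 0.98 × 0.999944 = 98.002%. With the cut-off moved so that Se = 70%, Sp = Φ(1.190 − 0.524) = 0.747 and accuracy = 0.014 + 0.732 = 74.6%.

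**Step 4: can accuracy tell models apart?** The same formulas give the best attainable accuracy, with sensitivity at that cut-off in brackets:

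| Rate | Flag nobody | AUC 0.70 | AUC 0.80 | AUC 0.90 | Spread, 0.70 to 0.90 |
|---|---|---|---|---|---|
| 2% | 98.00% | 98.00% (0%) | 98.00% (0.4%) | 98.10% (11%) | 0.1 points |
| 10% | 90.0% | 90.0% (0.5%) | 90.4% (11%) | 92.3% (38%) | 2.3 points |
| 20% | 80.0% | 80.3% (7%) | 82.6% (28%) | 87.3% (56%) | 7.0 points |
| 30% | 70.0% | 72.0% (22%) | 76.9% (45%) | 84.2% (67%) | 12.1 points |

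At 2%, going from a weak to a strong model changes about 0.00104 × 12,000 ≈ 12 classifications. At 20% to 30% accuracy does separate the models. The fixed 80/90 model shows the same pattern: it scores 89.0% against 90.0% for flag-nobody at a 10% rate, but 88.0% against 80.0% at 20% and 87.0% against 70.0% at 30%.

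**The case against.** The strongest reply is that the article does not commit to accuracy. Its wording allows accuracy as one example among others, in the same loose style it uses for the modelling methods. Log loss, AUC or calibration would all comply with the sentence, and a fuller list may be in an analysis plan that is not shown. This stands. The absence of a complete metric list is no finding, and a reader who infers that accuracy will be the sole or deciding criterion goes beyond the text.

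Three further limits also stand:

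- **Tuning.** A reader might infer that hyperparameters will be tuned on accuracy. The sentence on selection and tuning names no metric. Accuracy appears in the next sentence, about model fit, so the link is plausible but inferred.
- **Missed events.** A reader might infer that the chosen models would miss nearly all events. The low sensitivities in the working belong to a cut-off, and moving a cut-off does not alter how a model's probabilities rank women. The calculation shows that accuracy is uninformative at 2%. It does not show that a poor model would be chosen.
- **Purpose.** A reader might infer that the study's aim is defeated. The Abstract states the goal as a large sharable dataset for building algorithms. One example metric does not harm the dataset, and no accuracy criterion is stated for the treatment-regime work.

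It is also fair to say that the composites may be much commoner than 2%. The maternal one pools death, hemorrhage, several hypertensive disorders and infection.

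The objection does not make accuracy a suitable example. The article names a metric that does not match the stated product, a probability for risk stratification, and that is weakest for the rare outcomes it says drove the sample size.

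**Conclusion.** The point holds in a limited form. Accuracy is the only metric named for binary outcomes. For components near 2% it is nearly uninformative for comparing models: the no-model value is 98.0%, the best value at AUC 0.80 is about 98.0%, and AUCs from 0.70 to 0.90 differ by about 0.1 point. For outcomes at 20% or more this part of the problem largely recedes, and the article does not say where the composites lie. At every rate, accuracy judges labels at one cut-off and does not assess calibration or ranking, which risk stratification needs.

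The 98.0% benchmark is arithmetic and depends only on the rate. The model comparisons rest on the assumed binormal form and AUCs. Any practical harm depends on accuracy actually being used to choose models or report success, which the article permits but does not require. The change is worth making because the article points to an unsuitable metric and a better one is readily available.

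**What to change.** In the Predictive models paragraph, replace accuracy as the named metric for binary outcomes:

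1. Name a proper score (log loss or Brier score) for model selection and tuning.
2. Report AUC and calibration on the held-out test set.
3. For rare components, add precision-recall area, or sensitivity and PPV at prespecified risk thresholds. Threshold-based reporting is also where missed events and false alarms can be shown separately, since an unweighted log loss or Brier score assigns them no unequal clinical cost.
4. If accuracy is still shown, print 1 minus the prevalence beside it.

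The cost is a wording change and a little extra analysis. Follow-up is already complete, but no new data are needed: the held-out predicted probabilities that these measures use are already part of the plan.
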